### Survival analysis

Given the lack of epidemiological data on stage at diagnosis and outcome of treatment of cervical cancers detected in tribal vs non-tribal women through the national cancer registries, a survival analysis will be undertaken at the Vellore subsite to confirm the suspected late stage at detection and poor survival outcomes in the former group. Women with cervical cancer seen at CMC Vellore in the previous 10 years will be identified from hospital records, noting baseline characteristics (demographic and cancer type and stage) recorded during hospital visits. Their vital status will be obtained from case files and data linkages with the death records and routine health information system maintained for the primary care service areas, supplemented where necessary by active follow-up by health workers to document current vital status. With around 31 patients from the tribal study site and 46 belonging to our non-tribal study sites (rural and urban poor women), we will have 80% power to detect a hazard ratio of 2.5, assuming 5-year survival of other groups as 70% [34].

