### Quantitative

Numbers and proportions of screening and treatment activities and outcomes will be reported, based on the survey of facilities. Survival rates will be estimated, disaggregated by rural, tribal, and urban-poor cohorts of women with cervical cancer diagnosed in populations covered by primary care services of CMC Vellore, with adjusted hazard ratios for predictors of survival (Cox regression) and Kaplan-Meier survival curves.

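### The survival cohort is entered by a hospital visit in the last 10 years, not by date of diagnosis, which can bias the survival rates upward unless delayed entry is used

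*Protocol article*

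**What the plan says.** The Survival analysis section of the protocol article gives the case-finding rule: "Women with cervical cancer seen at CMC Vellore in the previous 10 years will be identified from hospital records". Baseline data are taken from the same records, "noting baseline characteristics (demographic and cancer type and stage) recorded during hospital visits". Vital status comes from case files and record linkage, "supplemented where necessary by active follow-up by health workers to document current vital status". No start of the survival clock is named.

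The section sizes the analysis thus: "With around 31 patients from the tribal study site and 46 belonging to our non-tribal study sites (rural and urban poor women"), followed by "we will have 80% power to detect a hazard ratio of 2.5, assuming 5-year survival of other groups as 70" per cent.

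The Quantitative section, under the Phase 1 data analysis, plans survival rates by rural, tribal and urban-poor group, Kaplan-Meier curves and Cox regression, in "cohorts of women with cervical cancer diagnosed in populations covered by primary care services of CMC Vellore". That phrase limits the cohort by place of residence. It sets no limit on the date of diagnosis, and delayed entry is not mentioned.

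**The concern.** A survival cohort assembled by a visit in a calendar window mixes two kinds of patient. Women diagnosed inside the window are followed from the start of their disease. Women diagnosed before it appear only because they survived to the window and came back. If the years they lived before entry are counted as follow-up at risk, the analysis adds time during which, by construction, none of them could have died. This is left truncation, and ignoring it pulls the Kaplan-Meier curve up.

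Survival rates by group are a stated output of this analysis, and the article justifies it by the absence of such data for tribal women. An overstated rate would understate the problem the analysis is meant to document. The comparison between groups is also exposed if the groups differ in how often long-term survivors return.

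**Working it through.** **The plan's own figure.** With 70% five-year survival in the reference group and a hazard ratio of 2.5, tribal survival is 0.70^2.5 = 41.0%. Expected five-year deaths are 46 × 0.30 + 31 × 0.590 = 13.8 + 18.3 = 32.1. With tribal share 31/77 = 0.403, the Schoenfeld statistic is √(32.1 × 0.403 × 0.597) × ln 2.5 = 2.55. Power is Φ(2.55 − 1.645) = 81.6% one-sided and Φ(2.55 − 1.96) = 72.1% two-sided. The stated 80% is therefore close to a one-sided 5% test. The article does not state the test level or sidedness. The figure neither supports nor weakens the point below; it supplies the 70% and 41%.

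**Model for the bias (assumed).** Constant rate of diagnosis; constant hazard λ; diagnoses reaching L years before the 10-year window; a fraction p of the women alive when the window opens is seen again; time counted from diagnosis with no delayed entry.

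- Non-tribal λ = −ln(0.70)/5 = 0.0713 per year; tribal λ = 2.5 × 0.0713 = 0.1783.
- Let S(u) = exp(−λu), A(u) = (10 − u) + p·u, and B(u) = [S(u) − S(L)]/λ. B covers earlier-diagnosed women who are counted at risk at time u although they had to survive beyond u to enter.
- Apparent hazard for u up to 5: h(u) = λ·S(u)·A(u) / [S(u)·A(u) + p·B(u)].
- Apparent five-year survival: exp(−∫h(u)du), u from 0 to 5.

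Worked case (non-tribal, L = 10, p = 1). At u = 0: A = 10, B = (1 − 0.49)/0.0713 = 7.15, so h = 0.0713 × 10/17.15 = 0.042. At u = 5: S·A = 7.0, B = (0.70 − 0.49)/0.0713 = 2.94, so h = 0.0713 × 7.0/9.94 = 0.050. Both are below the true 0.071. Integrating gives 79.7% against a true 70%.

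The earlier-diagnosed share of the cohort is q/(10 + q), with q = p·[1 − S(L)]/λ. In the same case this is 7.15/17.15 = 42%.

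| L (years) | p | Non-tribal (true 70%) | Tribal (true 41%) | Implied HR (true 2.5) | Earlier-diagnosed share, non-tribal / tribal |
|---|---|---|---|---|---|
| 5 | 0.10 | 70.7% | 41.8% | 2.51 | 4% / 3% |
| 5 | 0.25 | 71.5% | 42.9% | 2.52 | 10% / 8% |
| 5 | 0.50 | 72.7% | 44.5% | 2.54 | 17% / 14% |
| 5 | 1.00 | 74.5% | 47.0% | 2.56 | 30% / 25% |
| 10 | 0.10 | 71.8% | 42.9% | 2.55 | 7% / 5% |
| 10 | 0.25 | 73.9% | 45.3% | 2.61 | 15% / 10% |
| 10 | 0.50 | 76.4% | 48.5% | 2.69 | 26% / 19% |
| 10 | 1.00 | 79.7% | 53.1% | 2.79 | 42% / 32% |

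The implied hazard ratio is ln(tribal survival)/ln(non-tribal survival). Simulation under the same model agrees to within about half a point of survival. With p = 0 the bias is zero.

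**Unequal return (assumed).** With 50% of non-tribal and 10% of tribal survivors seen again, the implied hazard ratio is ln(0.429)/ln(0.764) = 3.15 for L = 10 and 2.74 for L = 5. With the fractions reversed it is 2.18 and 2.33.

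**After correction.** In simulation, restricting to women diagnosed in the window, or using delayed entry, returns about 70% and 41%. The entry time matters. When the return visit falls some time after the window opens (assumed mean delay 3 years, L = 10), entry at the opening of the window still leaves about 73% and 45%. Entry at the first visit gives 70% and 41%.

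**The case against.** The best defence is that *seen* is clinical shorthand for newly diagnosed. The section speaks of stage at diagnosis and of baseline characteristics, so an incident cohort is a natural reading. Time origin and delayed entry often sit in a full protocol or analysis plan, which is not shown, and both Kaplan-Meier and Cox methods can handle left truncation. This stands as far as the missing detail goes. It does not remove the point, because the article states an entry rule and that rule, as worded, lets in earlier-diagnosed survivors.

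It is also fair that sampling error is large here. Ignoring censoring, the 95% half-width is 1.96 × √(0.70 × 0.30/46) = 13 points for the non-tribal group and 1.96 × √(0.41 × 0.59/31) = 17 points for the tribal group. Most of the scenarios above are well inside that. A systematic error that a change of wording removes is still worth removing.

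A reader might infer three stronger things that the documents do not support:

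- *That survival will certainly be inflated.* This needs earlier-diagnosed women in the cohort, time counted from diagnosis, and no delayed entry; the article settles none of these. If time ran from the first visit in the window, women returning with relapse could even lower the estimate.
- *That the two sections define contradictory cohorts.* The Quantitative section limits by place, not by date, so the two are compatible, only unaligned.
- *That stage at detection will be biased toward early disease.* This is plausible, but no stage-specific survival is given and nothing here quantifies it.

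**Conclusion.** The point holds in conditional form. The stated entry rule admits women diagnosed before the window only if they survived to return. If survival is counted from diagnosis without delayed entry, the five-year rates are overstated by about 1 to 10 points in the non-tribal group and 1 to 12 in the tribal group. These ranges rest on constant incidence and hazard, a look-back of 5 to 10 years and return fractions of 10% to 100%, all assumed; the bias is zero if no such women are seen.

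The hazard ratio on which the analysis is powered stays between 2.5 and 2.8 under equal return. Equal return cannot be taken for granted, since the article itself describes its tribal populations as remote and poorly served. Under the unequal fractions tried, it ranges from about 2.2 to 3.15. The absolute survival rates are the main exposure, and the rule should be settled before the records are abstracted.

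**What to change.** In the Survival analysis section, name the date of first diagnosis as the time origin and choose one of two rules:

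1. Restrict entry to women first diagnosed within the 10-year window.
2. Keep all women seen, record each date of diagnosis and of first visit in the window, and enter earlier-diagnosed women into the risk set at that visit, in both the Kaplan-Meier and the Cox analyses.

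Use the same cohort wording in the Quantitative section, and state whether the 31 and 46 are incident cases.

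The change is a line or two of text, but rule 1 may not be cheap in patients. It lowers the counts by the share of earlier-diagnosed women, which the documents do not give. In the 10-year look-back scenarios, 25% return leaves 46 × 0.85 = 39 and 31 × 0.90 = 28 women; full return leaves 46 × 0.58 = 27 and 31 × 0.68 = 21. If the 31 and 46 are not all incident, the power statement would need redoing. Rule 2 keeps these women at the cost of slightly more abstraction and analysis work.

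### The 80% power for the tribal versus non-tribal survival comparison does not hold at two-sided 5% with the follow-up the design implies; it is about 69–76%

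*Protocol article*

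**What the plan says.** The Survival analysis section of the protocol article describes a retrospective comparison at the Vellore subsite. Its purpose is to confirm a suspicion that tribal women are diagnosed later and survive less well. On case finding it says: "Women with cervical cancer seen at CMC Vellore in the previous 10 years will be identified from hospital records". Vital status is traced to the present through case files, record linkage and, where needed, active follow-up by health workers.

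The size and power statement reads: "With around 31 patients from the tribal study site and 46 belonging to our non-tribal study sites", then "we will have 80% power to detect a hazard ratio of 2.5, assuming 5-year survival of other groups as 70" per cent. The section gives no alpha, sidedness, length of follow-up, number of deaths or formula.

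The Quantitative section plans survival rates by cohort, "with adjusted hazard ratios for predictors of survival (Cox regression) and Kaplan-Meier survival curves".

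Table 1 places the survival analysis in Phase 1 (year 1). The section on objectives and frameworks allots 9 months to the situational analysis.

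**The concern.** The power of a survival comparison is set by the number of deaths, not the number of women. The article gives enough to work out roughly how many deaths to expect. That number falls short of what 80% power requires under the usual reading of an unqualified power figure, which is two-sided 5%.

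At stake is how the result will be read. The analysis is framed as confirming poorer survival in tribal women. If the comparison is not significant, readers will take it as coming from an 80%-powered study, with a 20% chance of missing a 2.5-fold hazard. At two-sided 5% with the follow-up implied, that chance is about 24–31%.

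**Working it through.** **Inputs from the Survival analysis section.** Tribal n = 31; non-tribal n = 46; hazard ratio 2.5; 5-year survival 70% in the non-tribal women.

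**Assumptions added here, because the article does not state them.** Proportional hazards, exponential survival, 5% alpha (one- and two-sided), and the follow-up patterns below.

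**Derived quantities.**
- Tribal share p = 31/77 = 0.4026, so p(1−p) = 0.2405.
- ln 2.5 = 0.9163; its square is 0.8396.
- Tribal 5-year survival = 0.70^2.5 = 0.410.
- Non-tribal hazard = −ln(0.70)/5 = 0.0713 per year; tribal hazard = 2.5 × 0.0713 = 0.178 per year.

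**Reproducing the stated 80%.** With every woman followed five full years, deaths are 46 × 0.30 + 31 × (1 − 0.410) = 13.8 + 18.3 = 32.1. Schoenfeld power is Φ(√[d·p(1−p)]·ln HR − z).
- One-sided 5%: Φ(2.546 − 1.645) = 82%.
- One-sided 5%, diagnoses spread evenly over 10 years: 79% by Schoenfeld and 80% by Freedman.
- Simulated log-rank tests (20,000 runs), one-sided: 84% and 80% for these two patterns.

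So one-sided 5% reproduces the figure.

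**Deaths needed at two-sided 5%.** (1.960 + 0.842)² / (0.2405 × 0.8396) = 38.9. At one-sided 5% the requirement is 30.6.

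**Power at two-sided 5% under the follow-up the design implies.** With diagnoses spread evenly over a window of A years and F further years for everyone, the probability of death at hazard λ is 1 − [e^(−λF) − e^(−λ(A+F))]/(λA).

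| Follow-up | Expected deaths | Schoenfeld | Simulated log-rank |
|---|---|---|---|
| 5 years for every woman | 32.1 | 72% | 75% |
| Even diagnosis over 10 years, no extra time | 29.7 | 69% | 70–71% |
| Same, plus the whole 9-month phase | 33.2 | 74% | 76% |

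For the five-year pattern, Freedman (74%), a Wald calculation (73%) and a two-proportion comparison (72%) agree.

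**What would bring two-sided 5% back to about 80%.**
- 6 years for every woman: 36.4 deaths, 77% by Schoenfeld, 79% by Freedman, 80% simulated.
- 6.5 years for every woman: 38.3 deaths, 79% by Schoenfeld, 81% by Freedman.
- The 10-year window plus 2 further years: 38.4 deaths, 79% by Schoenfeld, 81% by Freedman.

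**Hazard ratio detectable with 80% power at two-sided 5%.** About 2.7 with five years for everyone (33.0 deaths, 79.9%). About 2.8 with even diagnosis over 10 years (30.7 deaths, 79.9%).

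**Precision at a true hazard ratio of 2.5.** 95% CI = exp(0.9163 ± 1.96/√[d × 0.2405]). This gives 1.23 to 5.06 with 32.1 deaths and 1.20 to 5.21 with 29.7.

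**The case against.** A reader might infer that the 80% is simply an arithmetic error. The document does not support that. It names no alpha or sidedness, its aim is worded in one direction, and one-sided 5% gives 79–84%. Nor can one say that a one-sided test is the sole route to 80%. The 70% five-year figure fixes the baseline hazard and is not a censoring time. Women are traced to current vital status, so some will have well over five years, and longer average follow-up or a case mix weighted to earlier diagnoses would reach 80% at two-sided 5%. All of this stands.

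The longer-follow-up route is nevertheless hard to reconcile with the design. Even accrual over 10 years gives a mean potential follow-up of about 5 years, recent cases cannot have 6, and crediting the whole 9-month phase adds only about 3.5 deaths (33.2 against 29.7). A case mix weighted to recent years would push the other way.

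It can also be said that a condensed article may leave alpha and sidedness to a fuller document. That is fair as to the omission alone. The point here is that a printed figure depends on a condition a reader would not assume.

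Finally, the sample is whatever the records hold, no trial-arm decision is tied to this p-value, and hazard ratios and Kaplan-Meier curves are already planned. This stands and limits the severity.

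**Conclusion.** At two-sided 5%, with the stated inputs and the follow-up implied by a 10-year case window analysed in year 1, about 30–33 deaths are expected against about 39 needed. Power is about 69–76%, a shortfall of roughly 4–11 percentage points. The stated 80% is right for a one-sided 5% test, or for a two-sided one with clearly longer average follow-up, and the article states neither.

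The result rests on exponential survival, proportional hazards and roughly even diagnosis over the window. Incomplete tracing and covariate adjustment in the Cox model are not counted, because the document gives no figure for either.

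Severity is minor to moderate: a relied-on figure needs its condition stated or its value restated, in one retrospective part of the formative phase.

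**What to change.** Restate the power sentence with alpha, sidedness, assumed follow-up and expected deaths.

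- **If two-sided 5%:** for example, with 31 and 46 women and about 30–33 expected deaths, power is about 70–75% for a hazard ratio of 2.5, or 80% for a hazard ratio of about 2.7–2.8.
- **If one-sided 5% was used:** keep 80% and say so.
- **If longer follow-up was assumed:** give the distribution of diagnosis dates and the resulting deaths, about 39 for 80% at two-sided 5%.

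Report the hazard ratio with its 95% CI (roughly 1.2 to 5.2 if the estimate is 2.5), as an estimate rather than as confirmation. Do not interpret a non-significant result as coming from an 80%-powered two-sided comparison.

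The cost is one sentence and possibly a slightly less favourable figure. No extra patients or data are needed.

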### Qualitative study

A qualitative study will be conducted among screening-eligible women and community members to understand characteristics of screened and unscreened women, barriers to accessing screening and treatment, and unintended adverse effects or benefits associated with screening, as well as preferences related to receiving information, HPV test on self-collected samples, location for screening, receiving results, and treatment.

Semi-structured in-depth interviews will be conducted for women with lived experiences of prior screening using VIA or Pap smear (both screen positive and negative women) in each site, with the number of interviews depending on data saturation. Two FGDs with 6–8 participants each will be conducted per site (2*5 = 10), among women who have not been screened, with one of the FGDs among those who are considered most hard to reach by the community themselves (e.g. extremely poor, widowed, lower caste). FGDs for other community members who are not part of the target group (males, older and younger women) will include participants recruited through community connections/health workers, including the hardest to reach groups as a separate group. A total of 20 such FGDs are expected to be carried out across the five sites (ten each among males and females).

### Qualitative study procedures

Participants will be interviewed at a private location at a time convenient to them, by trained staff, after obtaining written informed consent. All interviews and FGDs will be audio recorded, transcribed, and translated to English (from Miso/Tamil), with all personal identifiers removed. Interviews/FGDs will be led by a trained facilitator, providing basic information about HPV-based screening, including showing the swab and instructions for self-collection. The number of interviews/FGDs will depend on overall saturation of themes raised by participants.

## Details of data analysis planned for phase 1

*Narrative synthesis of documents* reviewed will be performed, describing (1) screening programme delivery, performance, and outcomes and (2) cancer service utilisation and treatment rates for women diagnosed with cervical cancer. Programme pathways and the interaction points for patients, providers, and services will be visually mapped. CFIR domains will be used to describe the barriers and facilitators.

### Qualitative data

Transcribed data will be analysed using thematic analysis using software (NVIVO, QSR International Pty Ltd.). In addition to codes defined a priori (deductive analysis), the transcripts will be assessed to identify any emerging themes (inductive approach).

### Quantitative

Numbers and proportions of screening and treatment activities and outcomes will be reported, based on the survey of facilities. Survival rates will be estimated, disaggregated by rural, tribal, and urban-poor cohorts of women with cervical cancer diagnosed in populations covered by primary care services of CMC Vellore, with adjusted hazard ratios for predictors of survival (Cox regression) and Kaplan-Meier survival curves.

## Phase 2—co-design workshop

A stakeholder workshop will be organised following analysis of phase 1 data to:Summarise and seek feedback about the results of phase 1,Seek information on issues that are unclear and/or lack adequate information,Share evidence-based knowledge (e.g. the evidence for self-collection, HPV-based screening and registry-based follow-up systems) and understand pros and cons of different approaches,Identify leverage points for positive change, using multiple scenario analysis. These scenarios explore ‘what if’ and acknowledge that there will be pros and cons of all options,Create a visual model of screening and treatment, aided by qualitatively coding the use of CFIR domains/construct terminology in the stakeholder workshops, following INSPIRE methodology [25] andObtain a shared commitment to the common goal of promoting an acceptable, feasible HPV-based screening programme.

The aim is to design HPV-based screening approaches that will best fit the local context in each type of setting, with maximal potential to impact cervical cancer incidence and mortality [25]. Key parameters that will be finalised for the trial will include where and how the offer of screening is made, where the test sample is collected, HPV assay/s type and location of testing (e.g. point of care or centralised laboratory), means of communicating the results, whether screen and treat will be used, clinical pathways for further assessment, and data items and flows for managing the implementation. Strengthening of the current VIA-based screening approach will also be considered as a possible comparator, depending on stakeholder discussions.

The steps in intervention development, followed in phases 1 and 2 of the study, will be reported according to the guidance for reporting intervention development studies in health research (GUIDED) checklist [35].

## Next steps—act strategically and evaluation

A cluster randomised trial will be done evaluating co-designed implementation approaches for HPV-based screening, in year 2 of the study, based on the arms finalised after the formative phase. The trial has been registered with the Clinical Trials Registry of India (CTRI/2022/04/042327), but exact implementation approaches/trial arms will be revised and finalised only after the initial formative phase. Hence, trial methodology will be published later. Implementation outcomes, effectiveness, and cost effectiveness, will be analysed, comparing HPV-based screening approaches to each other as well as the current VIA-based approach. Sustainability assessment will be done using the Intervention Scalability Assessment Tool (ISAT) [31] at a final stakeholder workshop.

## Discussion

WHO modelling analyses of strategies to eliminate cervical cancer as a public health problem in LMICs estimated that successful implementation at scale of girls-only vaccination, twice-lifetime HPV-based screening, with appropriate treatment of precancer and cancer, could avert 62 million deaths related to cervical cancer, in the next 100 years, with 9.9 million deaths averted in India alone [1]. What is urgently needed now is implementation research to determine exactly how countries can meet the WHO strategy’s 2030 scale-up targets for cervical screening (> 70% women aged 30–49 years are screened using a high-performance test, followed by appropriate treatment of at least 90% of cervical disease) [2]. This will require leveraging current workforce and primary health care structures and integrating the screening and treatment pathways into universal health care systems after identifying and addressing existing barriers.

Difficulty in ensuring follow-up assessment of screen-positives is a problem for any screening strategy that requires a second visit for treatment [12, 21]. An HPV-based screen and treat strategy has been found to have improved effectiveness and cost effectiveness compared to HPV testing followed by triage and treat, or VIA screen and treat strategies, in low-resource settings [36, 37], with the WHO strongly recommending it for resource limited settings [38]. However, currently, VIA, rather than HPV, is the test of choice for primary screening in the guidelines of the national programme, as well as of professional bodies, in India [39–41]. The national programme also promotes colposcopy and biopsy of VIA positive women, in spite of known challenges in scaling up of colposcopy and histopathology facilities in rural or hard-to-reach areas. Our formative phase will help inform whether an HPV-based screen and treat approach would be acceptable to women and stakeholders and which barriers are to be overcome to roll out such a programme, ensuring high participation of the tribal women and other vulnerable populations.

The protocol of the formative phase of our study illustrates the steps required to understand the system, ensuring that the concerns and needs of all stakeholders are identified prior to implementing a new programme. The health system evaluation will assess structural and dynamic fidelity of local implementation in comparison to national/state guidelines over time, and inform adaptations and changes to be implemented to support the transition to HPV-based cervical screening. Inclusion of geographically isolated tribal populations in this study, a group that constitutes 8.6% of the population of India and who face inequity in health care access and worse health indicators compared to non-tribal populations within their states, is a key strength of the study [42]. Studies reporting implementation outcomes of HPV-based cervical screening in such tribal groups are lacking in India and so is disaggregated data regarding the burden of HPV and cervical cancer mortality in such groups that are characterised by poor geographical accessibility, isolated forest or hilly location, and low education [28, 42]. One study from Udupi, Karnataka, reported 40.6% prevalence of HPV infection in tribal women aged 20–65 years [43] but did not report outcomes of follow-up and treatment, while another reported 12.9% prevalence of HPV among girls and women aged 9–25 years from central India, based on urine samples [44]. The study from Karnataka also showed lack of awareness of cervical cancer, early sexual activity, and multiple sexual partners, which could explain higher rates of HPV prevalence in even young girls [43].

Inclusion of vulnerable women from tribal groups, as well as urban slum dwellers, in our study is also in line with the Tamil Nadu State Health Policy Vision 2030 and the Tamil Nadu Health Systems Reform Program, which aim to provide focused interventions to these two groups [45].

The study brings together a team of leading health researchers and programme implementers from India and Australia, with experience in providing cancer screening and related services for vulnerable populations, along with IARC and RTI, collaborating with vulnerable communities, policymakers, and local health services. The research will also support postgraduate training opportunities using the infrastructure of the collaborating institutions, for capacity building for implementation research.

